## Abstract

**Background:** Major depressive disorder (MDD) is a serious public health problem with high lifetime prevalence (4.4–20%) in the general population. The monoamine hypothesis is the most widespread etiological theory of MDD. Also, recent scientific data has emphasized the importance of immuno-inflammatory pathways in the pathophysiology of MDD. The lack of data on the magnitude of brain neuroinflammation in MDD is the main limitation of this inflammatory hypothesis. Our team has previously demonstrated the relevance of [18F] DPA-714 as a neuroinflammation biomarker in humans. We formulated the following hypotheses for the current study: (i) Neuroinflammation in MDD can be measured by [18F] DPA-714; (ii) its levels are associated with clinical severity; (iii) it is accompanied by anatomical and functional alterations within the frontal-subcortical circuits; (iv) it is a marker of treatment resistance.

**Methods:** Depressed patients will be recruited throughout 4 centers (Bordeaux, Montpellier, Tours, and Toulouse) of the French network from 13 expert centers for resistant depression. The patient population will be divided into 3 groups: (i) experimental group—patients with current MDD (*n* = 20), (ii) remitted depressed group—patients in remission but still being treated (*n* = 20); and, (iii) control group without any history of MDD (*n* = 20). The primary objective will be to compare PET data (i.e., distribution pattern of neuroinflammation) between the currently depressed group and the control group. Secondary objectives will be to: (i) compare neuroinflammation across groups (currently depressed group vs. remitted depressed group vs. control group); (ii) correlate neuroinflammation with clinical severity across groups; (iii) correlate neuroinflammation with MRI parameters for structural and functional integrity across groups; (iv) correlate neuroinflammation and peripheral markers of inflammation across groups.

**Discussion:** This study will assess the effects of antidepressants on neuroinflammation as well as its role in the treatment response. It will contribute to clarify the putative relationships between neuroinflammation quantified by brain neuroimaging techniques and peripheral markers of inflammation. Lastly, it is expected to open innovative and promising therapeutic perspectives based on anti-inflammatory strategies for the management of treatment-resistant forms of MDD commonly seen in clinical practice.

Clinical trial registration (reference: NCT03314155): https://www.clinicaltrials.gov/ct2/show/NCT03314155?term=neuroinflammation&cond=depression&cntry=FR&rank=1

## Introduction

Major depressive disorder (MDD) is a serious public health problem (1) with high lifetime prevalence (4.4-20%) in the general population (2). Impairment of quality of life is comparable to chronic diseases such as low back pain, high blood pressure, or cancer (3, 4). MDD is considered a “deactivation of psychosocial function” (5). It usually appears as part of a complex picture of comorbidities that are most often not or hardly managed since they may not be recognized (6). Standard therapeutic strategies often fail in up to one-third of cases in everyday clinical practice (7). The definition of treatment-resistant depression varies in the literature. Nevertheless, it is characterized by the absence of significant symptomatic remission after two successive attempts with antidepressants of different pharmacological classes, well-conducted in terms of dosage and duration, whilst ensuring quality observation (at least 80% of treatments made during the period under consideration) (8, 9).

The monoamine hypothesis is the most widespread aetiological theory of MDD (10, 11). Hence, all available antidepressants primarily act by increasing monoamine neurotransmission (serotonin, dopamine, and noradrenaline) (12). Consequently, hypofunction of the brain monoamine systems is among the most critical neurochemical mechanisms implied in MDD.

Recent scientific data has emphasized the importance of immuno-inflammatory pathways in the pathophysiology of MDD based on 4 main observations. First, a high prevalence of depressive symptoms is observed in chronically ill patients treated with the pro-inflammatory cytokine interferon-alpha (13, 14). Second, there is a high frequency of depressive symptoms in patients suffering from autoimmune or chronic inflammatory diseases (15–18). Third, a significant association has been found between an increase in the inflammatory marker CRP and the subsequent onset of depressive symptoms (19–22). Fourth, there is an increase in circulating cytokines, both at peripheral and central levels, in depressed patients (23, 24). Amongst them, TNFα and IL-6 are most often increased. The results concerning IL-1β and IL-8 are more contradictory (23). These cytokines in the central nervous system (CNS) appear to result from microglia activation (25–27). Microglia activation is one of the characteristics of neuroinflammation (28). This contributes to the secretion of pro-inflammatory cytokines and nitric oxide (NO) (29). Microglia also contributes to the resolution of inflammation by releasing anti-inflammatory factors. This theory seems to be part of a broader bio-psycho-social conceptual framework. Indeed, it has largely been documented that exposure to stressful life situations such as social aggression, traumatic events of life, etc. known to increase the risk for the further development of depressive episodes, have a significant impact on the functioning of the Immune-Hypothalamo-pituitary-adrenal axis (30, 31). In addition, epigenetic mechanisms are presumably implicated in those functional alterations related to stress (31–33).

In parallel, neuroimaging data reveal that a wide range of brain regions and networks may be involved in MDD, reflecting the complexity and diversity of depressive states (34). Relationships with the inflammation status have been established. A negative correlation was found between plasma CRP levels and the thickness of the right medial prefrontal cortex in MDD. This negative association is secondary to enhanced production of neurotoxic metabolites such as quinolinic acid from the kynurenine pathway activated in inflammatory conditions (35). Savitz et al. have also found a strong relationship with the reduction in striatum volume in a MDD sample. Furthermore, striatal volume was correlated with several depression-related items primarily referring to “concentration difficulties,” “lassitude,” and “pessimism” (36). Numerous neuroimaging studies (37–41) in MDD have found functional abnormalities of those neuronal systems in MDD in either resting conditions or during specific challenging tasks. Also, peripheral inflammation is associated with the anatomical and functional changes that occur during MDD. Corticostriatal functional connectivity is decreased in depressed patients, which is negatively correlated with plasma levels of CRP and IL-6 (42).

The lack of data on the magnitude of brain neuroinflammation in MDD is the main limitation of the inflammatory hypothesis of MDD. Positron emission tomography (PET) imaging may provide a better understanding of the pathophysiology of MDD involving cases of CNS brain inflammation. The development of new radiotracers used in PET helps us to explore and quantify neuroinflammation in depressed patients. Many of these radiotracers specifically have as target the translocation protein (TSPO). The TSPO is an 18 kDa protein located in the outer mitochondrial membrane of microglia cells. Its density is measured by its distribution volume, which was shown to be increased when microglia is activated thereby contributing to consider changes in TSPO expression as a relevant biomarker for brain neuroinflammation (43). An initial study conducted by Hannestad et al. (44) using a carbonaceous radiotracer of TSPO (11-N-(2-methoxybenzyl)-N-(4-phenoxypyridin-3-yl)acetamide-[11C] PBR28) found no significant increase in TSPO in acute-phase MDD patients (*n* = 10). However, this study was conducted in a small group of patients who were clinically heterogeneous in terms of disease severity. Setiawan et al. recently reported a significant increase in the TSPO distribution volume in 20 patients with MDD in the right and left prefrontal cortex, anterior cingulate gyrus, and insula using a fluorinated marker ([18F] FEPPA) (45). To our knowledge, these are the first data to suggest that MDD is characterized by neuroinflammation found in specific brain regions implicated in the cognitive and emotional processing of environmental stimuli (45).

Our team recently demonstrated the relevance of [18F] DPA-714 as a neuroinflammation biomarker in humans with various neurological diseases (46). The [^18^F] DPA-714 and [^18^F] FEPPA molecules are two second radiotracers targeting TSPO (overexpressed microglial receptor with inflammation). The [^18^F]DPA-714 tracer has been studied extensively in humans and also in preclinical models (46–49). This tracer was also selected by the European consortium InMind (Imaging of Neuroinflammation in Neurodegenerative Diseases−7th Framework Programme of the EU—www.uni-muenster.de/InMind) as the gold standard for PET neuroinflammation imaging with TSPO. Since [^18^F] DPA-714 appears to be the currently preferred tracer for studying neuroinflammation in PET, it will be used in this study.

The primary objective of this study is to compare the TSPO distribution volume assessed in PET (DPA-714) between patients with moderate-to-severe MDD (“currently depressed group”) treated with antidepressants considered as ineffective (and before a new treatment strategy is initiated as recommended) and normal healthy subjects without any antidepressant treatment (“control group”).

The secondary objectives are to: (i) compare the TSPO distribution volume assessed by PET among the currently depressed patients, those in clinical remission but still being treated with antidepressants (“remitted depressed group”) and normal controls; (ii) correlate the severity of depressive symptoms, suicidal risk, and central neuroinflammation intensity evaluated by PET in the currently depressed group; (iii) measure the correlation between the distribution volume of PET-assessed TSPO and a series of structural (microstructural integrity, cortical thickness, intracerebral iron content) and functional (connectivity force of the default-mode network) MRI markers in the three subject groups; (iv) measure the correlation between the distribution volume of PET-assessed TSPO and the plasma concentrations of peripheral inflammatory markers in the three subject groups.

We formulated the following hypotheses: (i) Neuroinflammation in MDD can be measured by [18F] DPA-714; (ii) its levels are associated with clinical severity; (iii) it is accompanied by anatomical and functional alterations within the frontal-subcortical circuits that are highly involved in MDD; (iv) it is a marker of treatment resistance. If these hypotheses are confirmed, then this study will enhance our understanding of the role of these neuroinflammatory processes in MDD. This breakthrough could have a significant long-term therapeutic impact by developing more specific antidepressant drugs with potent anti-inflammatory action and/or medicines primarily targeting neuroinflammation.

## Subjects and methods

### Subjects

Our study will compare data collected in patients with moderate to severe MDD (“currently depressed group”, *n* = 20) treated unsuccessfully with classical antidepressants (SSRIs, SNRIs) before the initiation of a new antidepressant treatment according to good practice recommendations, with those included in two other study groups, comprising:
- non-depressed healthy volunteers (“control group”, *n* = 20), which enables us to control both the depression factor and the treatment factor for the characterization of neuroinflammation. They will be matched on age and gender to the experimental group of currently depressed patients;- depressed patients reaching clinical remission (“remitted depressed group”, *n* = 20) and still being treated with antidepressants, which allows us to control the depression factor. We hypothesize that the presence of an effective antidepressant treatment will contribute to demonstrate a significant decrease in neuroinflammation in those depressed patients. This group will be matched to the currently depressed group according to the class of antidepressant treatments (SSRIs, SNRIs), as well as age and gender.

### Eligibility criteria

The following inclusion criteria will be applied to all study groups: (1) men and women aged 25 to 55 years, (2) affiliated to a Social Security scheme, (3) able to understand the given instructions and information about the study design, and (4) have provided written informed consent. The currently depressed group will include patients: (1) meeting the DSM-5 criteria of MDD diagnosis, (2) experiencing significant depressive symptoms (as indicated by a score > 20 on the Montgomery and Asberg Depression Rating Scale, MADRS), (3) receiving an ineffective antidepressant treatment (a well-conducted treatment at an appropriate dosage for a minimum of 6 weeks), and (4) showing plasma antidepressant levels within the therapeutic range after at least 1 additional week of antidepressant treatment with unchanged dosage. The remitted depressed group will comprise patients: (1) meeting the DSM-5 criteria of MDD diagnosis, (2) achieving remission for at least 8 consecutive weeks according to the standard DSM-5 criteria (as indicated by a MADRS score <10), and (3) receiving antidepressant medications at a stable dosage for 1 week or more. The control group will include normal healthy subjects free from any current or past psychiatric conditions and without peripheral signs of inflammation (as indicated by circulating concentrations of hs-CRP <5 mg/L).

Patients with any of the following conditions are not eligible for both the currently depressed and remitted depressed groups: (1) woman who is pregnant (test at enrolment), parturient, or lactating, (2) persons deprived of their liberty by judicial or administrative decision, (3) persons unable to express consent, (4) subjects with an identified neurodegenerative condition or a psychiatric pathology other than MDD (bipolar disorder, chronic psychotic disorder, addictive disorder except for nicotine, obsessive-compulsive disorder, post-traumatic stress disorder), (5) subjects with a history of stroke, (6) subjects with an acute infectious pathology, or chronic or acute inflammatory diseases, (7) subjects with a history of autoimmune diseases, (8) subjects receiving long-term anti-inflammatory and immunosuppressive therapy, (9) subjects with antipsychotic treatment in the last 3 weeks prior to enrolment, (10) subjects with a prescription of diazepam, midazolam, chlordiazepoxide in the last week prior to enrolment, (11) subjects with contraindications to MRI or PET imaging, (12) subjects who refuse to be informed of an abnormality detected during MRI examination.

The exclusion criteria for the control group are: (1) a significant history of psychiatric or somatic disorders, (2) a current mental disorder, (3) an active suicidal risk, (4) an ongoing psychotropic treatment.

Depressed patients will be recruited throughout 4 centers (Bordeaux, Montpellier, Tours, and Toulouse) of the French network from 13 expert centers for resistant depression (50). The subjects of the control group will be included at clinical investigation sites working locally in close collaboration with each participating expert center.

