### Biological markers

The involvement of certain pro-inflammatory cytokines in MDD was highlighted in a meta-analysis by Dowlati et al. (64) and a recent literature review by Miller et al. (23). In these two articles, higher plasma concentrations of IL-6 and TNF-alpha were found in the MDD group than in the control groups without MDD.

The biological marker assessment will involve measuring the concentration of peripheral inflammation markers that are circulating cytokines including IL-6 and TNF-alpha, especially. For each research site, samples will be taken at the Clinical Investigation Center for all subjects.

Also, hs-CRP will be assayed on the pre-screening day as part of the usual follow-up of patients and as part of the enrolment visit for volunteers in the control group (exclusion criteria for volunteers in the control group showing hs-CRP levels > 5 mg/L indicating a significant inflammatory state). All the blood samples will be collected in the morning in order to limit the impact of circadian rhythm on the measurement of inflammatory markers.

The samples will be stored by the Clinical Investigation Centers associated with each expert center before being sent to the hospital departments involved in the determination of peripheral cytokine levels (IL-6 and TNF alpha) at the end of the study.

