### Risk benefit balance

No direct individual benefit can be expected for subjects participating in this study. The therapeutic modalities used in these patients will not be altered by their participation in the study or by the results. Strict compliance with the inclusion and exclusion criteria will ensure there are no foreseeable risks for persons participating in this study. The imaging modalities used (MRI and PET) do not involve any foreseeable risk when patients presenting a contraindication to one or other of these examinations are not included according to the aforementioned inclusion/exclusion criteria. The principal investigator must constantly monitor, assess, and document risks and ensure that they can be managed satisfactorily.

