### Experimental procedures (Table 1)

#### Preselection

Patients in both the currently depressed and remitted depressed groups will be preselected during their medical follow-up within each participating research site. Investigators will inform the patient and answer all questions about the purpose, nature of constraints, foreseeable risks, and expected benefits of the present research. They will also specify the rights of the patient regarding research and will verify the eligibility criteria. A copy of the Information/Consent form will then be given to the patient. Healthy volunteers for the control group will be invited by phone to participate into the study by a Clinical Investigation Centre clinical research associate. A copy of the information leaflet will be sent to them, giving them sufficient time to consider their participation.

**Table 1 T1:** Summary of INFLADEP design.

	**Preselection**	**Enrolment visit D0**	**Assessment visit D7 (± 5 days)**
Patient information	✓	✓	
Collection of informed consent		✓	
Clinical examination^1^ – Validation of eligibility criteria		✓	
Collection of blood samples^2^		✓	
MRI examination			✓
PET examination			✓
Questions about concomitant treatments		✓	✓
Search for AE/SAE		✓	✓

1 *Clinical examination: discussion with doctor, MADRS, BAS, C-SSCR, MINI surveys*.

2 *To measure CRP levels in healthy volunteers and biological markers (TNF-alpha, IL-6), TSPO phenotype in all subjects, beta-HCG for women of childbearing age*.

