#### Enrolment visit

After obtaining the subject′s consent, a clinical examination will be performed to verify the eligibility criteria of the potential study participants along with the collection of psychiatric and somatic history, and current treatments. This clinical examination will include MINI (Mini International Neuropsychiatric Interview) (Appendix 5), which consists of a short, structured clinical interview that allows investigators to diagnose past and current psychiatric disorders according to the DSM (65), which is an exclusion criterion for subjects in the control group. This visit will also involve conducting psychometric assessments (MADRS, BAS, C-SSCR).

A blood sample will be taken to measure hs-CRP levels (inclusion criterion for the control group). This sample will also be used to measure IL-6 and TNF-alpha if the subject is included in the study. All the samples will be taken in the morning to take into consideration, as much as possible, the effects of circadian rhythm on circulating inflammatory biomarkers. Thereafter, an appointment will be scheduled for the assessment visit depending on the availability of the subject and the different technical platforms, at 7 ± 5 days following the inclusion visit.

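### hs-CRP, a secondary outcome to be correlated with PET in all three groups, is timed and range-limited differently in patients and controls, and the exclusions that apply to controls need reconciling

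*Protocol article*

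**What the plan says.** **Cap.** Under Eligibility criteria, controls must be "without peripheral signs of inflammation (as indicated by circulating concentrations of hs-CRP <5 mg/L". Neither patient group has an hs-CRP limit. The Enrolment visit section also treats the cap as a control inclusion criterion. The Biological markers section words it as an exclusion above 5 mg/L, so a value of exactly 5 is unassigned.

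**Timing.** The Biological markers section states that "hs-CRP will be assayed on the pre-screening day as part of the usual follow-up of patients", but "as part of the enrolment visit for volunteers in the control group" for controls. Footnote 2 of Table 1 gives the purpose of the D0 blood sample as "To measure CRP levels in healthy volunteers and biological markers (TNF-alpha, IL-6), TSPO phenotype in all subjects, beta-HCG for women of childbearing age". The Enrolment visit section says "A blood sample will be taken to measure hs-CRP levels (inclusion criterion for the control group"), without making clear whether patients are assayed then too. PET takes place at D7 ± 5 days.

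**Use.** The Outcomes section lists hs-CRP with IL-6 and TNF-alpha as a secondary outcome. Secondary objective (iv) and the section Analysis of all data correlate the peripheral markers with PET in all three groups.

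**Exclusions.** The twelve-item list, which includes pregnancy and lactation, acute infection and inflammatory disease, autoimmune history, long-term anti-inflammatory and immunosuppressive therapy, and MRI or PET contraindications, is stated for the two patient groups. A separate four-item list follows: "The exclusion criteria for the control group are: (1) a significant history of psychiatric or somatic disorders", then current mental disorder, active suicidal risk and ongoing psychotropic treatment. The Risk benefit balance section says imaging carries no foreseeable risk "when patients presenting a contraindication to one or other of these examinations are not included according to the aforementioned inclusion/exclusion criteria".

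**The concern.** There are three linked problems.

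1. **Secondary objective (iv).** A marker that can change over days is measured at an unstated distance from PET in patients and within 12 days of it in controls. The control range is also cut at 5 mg/L. A difference between groups in the hs-CRP/PET correlation could then come from timing or truncation rather than biology.

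2. **Primary contrast.** The study compares neuroinflammation between depressed subjects and controls, yet only controls are screened on a peripheral inflammation marker, and only patients have explicit exclusions for infection, inflammatory disease and anti-inflammatory treatment. The groups are selected differently on something close to the quantity under study.

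3. **Internal consistency.** The safety statement covers everyone in the study and relies on the eligibility criteria. As written, the control list names neither pregnancy nor an imaging contraindication, although controls also receive the tracer, PET and MRI.

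**Working it through.** **1. Interval from hs-CRP to PET**

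- Controls: assayed at D0, PET at D7 ± 5. The interval is 7 − 5 = 2 to 7 + 5 = 12 days.
- Patients: assayed on the pre-screening day. The interval is those 2 to 12 days plus the time from pre-screening to D0, which the document does not state.
- IL-6 and TNF-alpha: drawn at D0 in all subjects, so the problem is confined to hs-CRP.

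**2. The plan's effect size, for scale**

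The sample size section gives 20 per group, 80% power and means of 12.3 and 9.3 ml/cm³ (difference 3.0), but no SD, so the 80% cannot be reproduced. Solving backwards at two-sided 0.05:

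- Normal approximation: SD = 3.0 / [(1.960 + 0.842) × √(2/20)] = 3.39, so d = 0.89.
- t-test: d = 0.91, SD = 3.30.

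These are implied values, not stated ones.

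**3. Size of the cap's effect on the primary contrast**

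The only CRP distribution figure in the document is in the Discussion: 16% of depressed patients above 3 mg/L. The share above 5 mg/L is not given, and nothing is given for controls. Assumptions:

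- hs-CRP is log-normal with the 16% applied to controls (probably too high for healthy volunteers);
- geometric SD (GSD) is 2 to 4;
- log hs-CRP and TSPO volume correlate at ρ = 0 to 0.5.

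Formulas: z₅ = 0.994 + ln(5/3)/ln(GSD); share above the cap q = 1 − Φ(z₅); downward shift in the control mean of log hs-CRP λ = φ(z₅)/Φ(z₅) in SD units; shift in the PET contrast = ρλ.

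| GSD | z₅ | q | λ | ρ = 0 | ρ = 0.3 | ρ = 0.5 |
|---|---|---|---|---|---|---|
| 2 | 1.731 | 4.2% | 0.093 | 0 | 0.028 | 0.047 |
| 2.5 | 1.552 | 6.0% | 0.127 | 0 | 0.038 | 0.064 |
| 3 | 1.459 | 7.2% | 0.148 | 0 | 0.044 | 0.074 |
| 4 | 1.363 | 8.6% | 0.173 | 0 | 0.052 | 0.086 |

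The shift is 0 to 0.086 SD. The standard error of the contrast is √(2/20) = 0.316 SD, so the largest shift is 0.086/0.316 = 27% of one standard error. It is 0.086/0.909 = 9.5% of the implied effect. A nominal 5% test (noncentral t, 38 df) would have a type I error of 5.0% to 5.8%.

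Stretching the share above the cap to 16% with ρ = 0.5 gives 0.145 SD, or 0.145 × 3.39 = 0.49 ml/cm³ (16% of 3.0), and a type I error of 7.4%.

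**4. Range restriction in controls**

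With u the ratio of the truncated to the full SD, u² = 1 − z₅λ − λ². Over the table, u = 0.91 down to 0.86. The correlation seen in controls is ρu/√(1 − ρ² + ρ²u²):

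- ρ = 0.3 becomes 0.28 to 0.26;
- ρ = 0.5 becomes 0.47 to 0.44.

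The attenuation is modest, but it affects controls only.

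**5. Exclusions side by side**

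| Item | Patient list | Control list | Partial cover for controls |
|---|---|---|---|
| Pregnancy, lactation | named | not named | beta-HCG test at D0 (pregnancy only), with no written criterion acting on it |
| MRI or PET contraindication | named | not named | technician's checks, MRI only |
| Acute infection | named | not named | hs-CRP cap, indirectly |
| Anti-inflammatory or immunosuppressive therapy | named | not named | healthy status, indirectly |
| Stroke, autoimmune history | named | not named | significant somatic history |

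**The case against.** The strongest objection concerns the primary contrast. A reader might infer that the cap biases it towards finding a difference. The documents do not support that:

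- No correlation between hs-CRP and TSPO is given. The Discussion reports that the earlier PET study found no relationship between neuroinflammation and peripheral markers, and at ρ = 0 there is no bias.
- The 16% figure describes depressed patients. Controls must be healthy and free of significant somatic history, so fewer would be expected above 5 mg/L.
- Excluding infection, inflammatory disease and autoimmune history explicitly in patients trims inflamed patients, which acts against the cap. The net direction is therefore undetermined.
- Leaving patients uncapped is defensible. The Discussion says inflammation occurs in a subset of depressed patients, and a cap would remove that subset.

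All of this stands and limits the primary-contrast point to a possible, small effect.

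On measurement, the Enrolment visit text may mean that hs-CRP is assayed at D0 in everyone, and the analysis section does not say that the groups will be pooled. The first possibility makes this a contradiction to resolve. The second does not remove the unknown lag within the patient groups.

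On safety, a reader might infer that controls are unprotected. That goes too far: beta-HCG is listed for women of childbearing age without a group limit, MRI checks apply to the subjects scanned, and a condensed article may shorten a list. What remains is that the article gives a separate, complete-looking control list and then relies on criteria that are not in it.

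**Conclusion.** The point holds in a limited form. The firm part concerns secondary objective (iv): two places take hs-CRP at different times in patients and controls, a third is ambiguous, the patients' interval to PET is unstated, and only controls are range-restricted. This follows from the text and needs no assumption.

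The groups are also selected differently on inflammation, which could affect the primary contrast. The cap alone would contribute about 0 to 0.09 SD, against a standard error of 0.32 SD. That range rests on an assumed 4 to 9% of controls above the cap and assumed correlations of 0 to 0.5. With the opposing patient-only exclusions, no direction can be claimed, and the result does not show that the primary comparison is invalid.

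The sections on eligibility, biological markers, Table 1, enrolment and risk benefit balance do not agree on which criteria cover controls, and must be reconciled.

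**What to change.** 1. **Assay.** Measure hs-CRP in all 60 subjects from the D0 morning sample already drawn, and use that value for the correlations. Align the Biological markers section, Table 1 footnote 2 and the Enrolment visit section. Cost: about 40 extra assays (two patient groups of 20) on existing blood.
2. **Reporting.** Give the hs-CRP/PET correlations by group and note that control values are restricted by the cap. No cost.
3. **Sensitivity analysis.** Repeat the primary contrast among subjects with hs-CRP below 5 mg/L in both groups. It uses fewer subjects and may remove part of the inflammatory phenotype, so it is supportive only.
4. **Reconciliation.** State which exclusions apply to controls as regards pregnancy and lactation, MRI or PET contraindication, acute infection, and anti-inflammatory or immunosuppressive therapy, and make the Risk benefit balance statement agree. Word the cap once, as inclusion or exclusion, so that exactly 5 mg/L is assigned. Cost: wording only.
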